### Who will take informed consent {26a}

All participants provide informed consent with the study coordinator prior to participating.

### Additional consent provisions for collection and use of participant data and biological specimens in ancillary studies {26b}

This trial does not involve collecting biological specimens.

### Interventions

#### Explanation for the choice of comparators {6b}

To evaluate the effects of estradiol while taking into account possible placebo effects, estradiol treatment is being compared to placebo treatment.

#### Intervention description {11a}

Participants will be randomized to either a 3-week estradiol (100 μg/day, via Climara® patch, or its generic) or placebo treatment. Four weekly clinical assessments will be conducted (baseline, week one, week two, and at the end of treatment) to assess changes in anhedonia and psychosis symptoms as well as blood serum levels of estradiol. Furthermore, participants will complete PET-MR scans at baseline and the end of treatment to examine neural and molecular responses to rewards.

#### Treatment arms

The estradiol treatment group will receive 100 μg/day of estradiol via the Climara® patch (or its generic) for 3 weeks, with weekly patch placement by the study coordinator. The same procedures will be used for the administration of the placebo patch. Upon completion of the 3-week protocol and post-treatment outcome measurement, participants in the estradiol group will receive 1 week of micronized progesterone at 200 mg/day, administered via the Prometrium® oral capsules (or its generic) combined with an additional week of estradiol (0.1mg/day, Climara® patch, or its generic). Study drugs and placebo patches will be maintained in the UNC Pharmacy Storeroom and dispensed by the UNC IDS to the study coordinator following the participant’s consent and eligibility assessment.

#### Dose justification

The Climara® patch is an FDA-approved treatment for menopausal and postmenopausal women experiencing vasomotor and genitourinary symptoms, with dosage ranging from 25 to 100 μg/day [48]. While estradiol treatment is not currently FDA-approved for treatment of perimenopausal affective disorders, there is empirical support for the efficacy at doses ranging from 100mcg/day [49] to 0.5mg/day [50]. Furthermore, to minimize adverse side effects, a biologically relevant dose will be administered for a short window. While adverse effects may be associated with longer duration usage in older, postmenopausal women [51], the current protocol is expected to pose minimal risk to participants [8].

#### Criteria for discontinuing or modifying the allocated intervention {11b}

Participants are free to withdraw from the study at any time, and this right will be reviewed during the consenting process. Investigators may discontinue study participation prior to completion of treatment for the following reasons: (1) intervention non-compliance; (2) the participant is lost-to-follow-up; (3) a medical condition or situation arises where continued participation is contraindicated; (4) a condition develops or an event occurs that meets exclusion criteria; (5) suicidal thoughts, plans, or intent is expressed; (6) or there are any other concerns about continued participation. In the case of severe mood symptoms or suicidal thoughts, the first three items on the Colombia-Suicide Severity Rating Scale will be administered by a member of the research team. If the participant expresses active suicidal ideation within the past week or expresses concerns about their ability to continue in the study, they will be evaluated by a licensed clinical psychologist or psychiatrist and will be discontinued from the study protocol. If symptoms are deemed otherwise unmanageable, inpatient admission to the university hospital’s psychiatry department will be arranged.

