#### Safety assessments

A baseline medical health assessment is conducted prior to clearing participants for treatment. This includes blood panels and a pelvic exam/PAP test done by the study gynecologist or the participant’s personal provider if they choose. If the participant has had a pelvic exam/PAP test completed within 3 years prior to enrollment, a review of medical records can take the place of an updated exam. Participants must show no evidence of exclusionary conditions and have no history of abnormal labs or resolved abnormal labs as verified by additional testing and treatment. Furthermore, prior to each PET-MR visit, participants will complete a pregnancy test and MRI screening form to ensure there are no contraindications to scanning.

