#### Relevant concomitant care permitted or prohibited during the trial {11d}

To be eligible to complete the study, participants must not be taking any psychotropic medication or supplement that is known to alter the mood. Study participants who elect to begin taking such medications or supplements during the 3-week treatment window will be discontinued from the study.

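### A woman with active suicidal ideation but no intent or plan is eligible at entry, yet already meets the mandatory stopping rule

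*Protocol article*

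**What the plan says.** **Entry.** In the Protocol article, the exclusion list under Eligibility criteria {10} has one item on suicidality. It removes women with an attempt in the preceding year, and women whose active ideation comes with intent or a plan. Active ideation without either is not listed.

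**Stop.** Criteria for discontinuing or modifying the allocated intervention {11b} has two layers. The first is a numbered list of reasons for which investigators may stop a participant. One reason is the expression of suicidal thoughts; another is that "a condition develops or an event occurs that meets exclusion criteria". The second layer is compulsory. It opens with "If the participant expresses active suicidal ideation within the past week", adds a participant's own concern about being able to continue as an alternative trigger, and concludes that "they will be evaluated by a licensed clinical psychologist or psychiatrist and will be discontinued from the study protocol".

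**Sequence.** Under Concealment mechanism {16b}, randomisation follows the determination of eligibility. Under Intervention description {11a}, "participants will complete PET-MR scans at baseline and the end of treatment". Under Treatment arms, patches are given for 3 weeks, "with weekly patch placement by the study coordinator".

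**The concern.** A stop that is stricter than the entry rule makes sense when it reacts to deterioration on treatment. This one can be met by a state that has not changed since screening. Staff who follow both rules to the letter would enrol a woman and then be obliged to remove her for something the entry rule allowed.

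What is at stake is participant safety and avoidable exposure: a radiotracer scan and study medication given to someone who already meets the trial's own stopping condition. There is a smaller analytic cost. Under Statistical methods {20a}, the mechanistic hypotheses use a per-protocol set that requires both scans and the full 3 weeks of treatment, so a woman stopped early drops out of the treatment-effect and change analyses. Her baseline scan may still serve the baseline correlations of the first objective, and her clinical scores remain in the intent-to-treat analysis.

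**Working it through.** No sample size, alpha or event rate enters this point, so the check is a comparison of the two rules.

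**Step 1: the rules as conditions.** Let A be active ideation in the past week and I be intent or a plan. For women with no attempt in the past year, entry excludes A together with I, and the compulsory stop applies to A once it is expressed.

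| State | Eligibility criteria {10} | Compulsory stop in {11b} | Consistent? |
|---|---|---|---|
| No A | eligible on this item | not met | yes |
| A with I | excluded | met | yes |
| A without I | eligible on this item | met when expressed | no |

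The third row is the conflict.

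**Step 2: does another criterion close the gap?** The inclusion criteria concern age, reproductive stage, anhedonia score and psychosis score. The remaining psychiatric exclusions concern earlier Axis I disorder, hospitalised mood episodes, current mania and substance use. None removes a woman because of active ideation without intent or plan. The discretionary reason that "a condition develops or an event occurs that meets exclusion criteria" does not reach her either, since her state does not meet an exclusion.

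**Step 3: is the stop really compulsory?** The numbered list is discretionary. The sentence containing "they will be evaluated by a licensed clinical psychologist or psychiatrist and will be discontinued from the study protocol" is not. A clinician's evaluation comes first, but the text does not make removal depend on its result.

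**Step 4: possible exposure per affected woman.** The inputs are 15 mCi total radioactivity per scan (Mechanistic outcomes), one baseline scan before treatment ({11a}), and weekly patches over 3 weeks at 100 μg/day or placebo (Treatment arms). Replacements for patches that fall off are ignored.

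- Stopped at screening, before the scan: 0 scans, 0 patches.
- Stopped in treatment week *k*, with *k* = 1, 2 or 3: 1 scan and *k* patches.

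The range is therefore 0 to 1 scan and 0 to 3 patches. The document gives no rate for this kind of ideation, so no trial-wide total can be computed.

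**The case against.** The best defence is that she would usually be found and removed before any exposure. Staff cannot apply the entry exclusion without asking about ideation, and screening includes a structured clinical interview. The compulsory stop speaks of the study protocol and is not limited to the period after the first patch. This stands, and it makes exposure a possibility, not a certainty. It does not remove the conflict, because she would then be declared eligible and be due for removal at the same moment.

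A second defence is that a stop stricter than entry is a cautious choice and not wrong in itself. That is true in general. It is weaker here because the rule asks for no change from entry.

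Three stronger readings are tempting, and the document does not support them.

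- **Ideation is the only stop that does not match an exclusion.** The section on concomitant care {11d} does pair an entry rule, "participants must not be taking any psychotropic medication or supplement that is known to alter the mood", with a stop, "Study participants who elect to begin taking such medications or supplements during the 3-week treatment window will be discontinued from the study". However, the exclusion list in {10} is wider on medication, since it also names hormonal preparations and drugs whose mood effects are unknown. The compulsory sentence in {11b} also stops women who voice concern about continuing, which matches no exclusion. Stops and exclusions are not aligned one to one in this article.
- **Suicidality is never assessed on a schedule.** The text of {11b} describes the rating-scale items as given when severe mood symptoms or suicidal thoughts arise. The schedule of assessments is a figure that is not shown, so nothing can be said about scheduled use.
- **The trial loses power.** No rate is available, and none is assumed.

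**Conclusion.** The point holds as a conflict between two explicit rules. It is not a complaint about missing detail: both rules are stated, and they disagree for women with active ideation but no intent or plan. Such a woman is either eligible and immediately removable, or she may receive one scan and one to three patches before being stopped and lost to the per-protocol mechanistic analyses. A reader might infer that such women will in fact be scanned and dosed; the document supports only that they could be.

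The conclusion assumes that the intent-or-plan qualifier in the exclusion means what it says, and that the stop applies without such a qualifier. The number affected is unknown and probably small, and no stated sample-size or power figure changes. Severity is minor.

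**What to change.** Reword the exclusion in Eligibility criteria {10} so that it covers a suicide attempt in the preceding year, or active ideation in the preceding week whether or not there is intent or a plan. Entry then matches the compulsory stop. Confirm it at the existing eligibility determination, before the baseline scan and randomisation. If the scan may fall more than a week later, the question can be repeated at the contact where, under Safety assessments, "prior to each PET-MR visit, participants will complete a pregnancy test and MRI screening form".

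Limiting the stop to new or worsening ideation would also remove the conflict, but it would loosen a safety rule, so tightening entry is preferable.

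The cost is a wording amendment with IRB approval and DSMB review, a question added to an existing contact if it is not already asked there, and a slightly smaller eligible pool. No new visit is needed.

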#### Safety assessments

A baseline medical health assessment is conducted prior to clearing participants for treatment. This includes blood panels and a pelvic exam/PAP test done by the study gynecologist or the participant’s personal provider if they choose. If the participant has had a pelvic exam/PAP test completed within 3 years prior to enrollment, a review of medical records can take the place of an updated exam. Participants must show no evidence of exclusionary conditions and have no history of abnormal labs or resolved abnormal labs as verified by additional testing and treatment. Furthermore, prior to each PET-MR visit, participants will complete a pregnancy test and MRI screening form to ensure there are no contraindications to scanning.

#### Strategies to improve adherence to interventions {11c}

Participants are instructed to contact the study team immediately if their patch begins falling off so that a new, blinded patch can be placed.

#### Relevant concomitant care permitted or prohibited during the trial {11d}

To be eligible to complete the study, participants must not be taking any psychotropic medication or supplement that is known to alter the mood. Study participants who elect to begin taking such medications or supplements during the 3-week treatment window will be discontinued from the study.

#### Provisions for post-trial care {30}

No harm is anticipated so there are no provisions prepared.

### Outcomes {12}

#### Mechanistic outcomes

The primary mechanistic endpoint in this trial will be neural and molecular response to rewards using simultaneous PET-MR, which will be measured at baseline and at the end of treatment. Scans will be collected on a Siemens Biograph mMR scanner. A whole-brain, T1-weighted MPRAGE image will be collected (1mm isotropic, TR=2400ms, TE=2.13ms). A whole-brain T2*-weighted BOLD sequence will be used for the acquisition of fMRI task data (3mm isotropic, TR=3000 ms, TE=30ms). Simultaneous acquisition of PET data will occur using [^11^C]raclopride PET imaging to estimate D2 and D3 receptor occupancy at baseline and during reward conditions. A bolus plus infusion protocol will be used with the following parameters: K_bol_=70 min, total radioactivity=15 mCi, mass dose=10 μg (specific radioactivity at time of bolus > 0.4 Ci/μmol). Listmode 3D emission data will be acquired from bolus administration through scan duration. The study will also acquire Siemens proprietary MR attenuation maps optimized for head imaging with a bone compartment to be used for attenuation correction.

This study uses a version of the monetary incentive delay (MID) task (for a review, see [52]), modified for PET-MR acquisition [53]. The task consists of a neutral block during which no monetary rewards are delivered, followed by reward blocks where varying magnitudes of rewards are delivered. Based on each participants’ reaction time performance, the task is programmed to code approximately 75% of responses as successful. Task trials consist of (1) the presentation of a blue polygon cue, followed by (2) the presentation of a green circle target stimulus cueing the participant to respond with a speeded button press, and then (3) the presentation of an outcome. For the neutral block, no monetary outcomes are delivered; rather, a gray rectangle is presented indicating a successful trial with no reward. Other outcomes include trial performance feedback (e.g., “Too Fast!” “Too Slow!” or “No Response!”). For reward blocks, task trials use the same structure, with a few minor differences. Instead of a stable blue polygon cue, different polygon cues are presented (e.g., square, triangle, pentagon, hexagon), which are associated with specific reward outcomes (e.g., no reward, 50 cents, one dollar, five dollars). Polygon cue-reward associations remain stable across trials. Thus, reward blocks capitalize on associative learning to optimize dopamine response to rewards [54]. Furthermore, compared to other versions of the MID task, a higher percentage of reward trials (75%) deliver reward outcomes, and many large rewards ($5) are offered, to increase reward anticipation response [55]. Consistent with the neutral block, for unsuccessful trials, performance feedback is delivered (e.g., “Too Fast!” “Too Slow!” or “No Response!”) in lieu of reward outcomes (e.g., no reward, 50 cents, one dollar, five dollars). The reward block begins approximately 40 min after [^11^C]raclopride bolus injection to allow for target/reference stabilization. This 40-min baseline acquisition period is used to estimate baseline binding potential.

For analysis of fMRI reward-related activation, functional data will be preprocessed, including motion correction, slice timing correction, normalization, and spatial smoothing. Event onsets will be convolved with a double-γ hemodynamic response function to model task-related activation. The primary task contrasts of interest will probe activation in reward versus neutral trials modeled separately during anticipation and outcome phases of the task. An a priori region-of-interest approach will be used in group-level analyses. Exploratory whole-brain analyses will also be conducted. All analyses will use a cluster-forming threshold of *p*<.001 and a cluster-corrected threshold of *p*<.05. With respect to molecular response to rewards estimated via PET, 1-min framewise post-scan reconstruction will be conducted. Motion correction will be applied using mutual information registration with a mid-frame reference. Binding potential will be estimated as the ratio of selectively bound ligand to non-displaceable ligand at tissue equilibrium. A dynamic occupancy model will be used to assess changes in binding potential secondary to dopamine release. Baseline binding potential (BP_ND_) and task-related changes in BP_ND_ (ΔBP_ND_) will be calculated using time-activity curves for regions of interest via a simplified reference tissue model (e.g., 3-parameter, single-exponential fit to the time activity curve). Non-vermis cerebellar regions will be used as the reference tissue.

Primary measures of neural activation will be estimated using mean percent signal change for the reward versus neutral contrast during anticipation. The primary molecular measures estimated via PET will include the average baseline dopamine binding potential and task-related changes in binding potential. For both neural and molecular measures, regions of interest will include the nucleus accumbens, caudate nucleus, and putamen. In addition, we will conduct exploratory fMRI analyses of activation in medial prefrontal regions during reward outcome processing.

#### Clinical outcomes

Clinical outcomes will include collecting measures of anhedonia (the SHAPS) and psychosis (the BPRS) symptoms.

### Participant timeline {13}

Figure 1 depicts the study timeline.

**Fig. 1 Fig1:**
[figure not shown]
Study timeline

### Sample size {14}

For the first study objective, correlation analyses will be used to examine associations between baseline clinical measures (anhedonia and psychosis) and neural markers (striatal BOLD activation and baseline/reward-related dopamine release). Power analysis suggests that a sample of 85 participants will yield approximately 80% power to detect small-to-medium effects (smallest detectible *r*=.27) at *α*=.05, which is consistent with our in-house pilot data. With respect to the study’s second objective, longitudinal mixed models will be used to examine the effects of estradiol versus placebo on (1) symptom trajectories measured across four timepoints and (2) neural/molecular markers across two timepoints. A sample of 85 participants will yield 80% power to detect small-to-medium effects, with the smallest detectible effect *f*^2^=.05 for clinical outcomes and *f*^2^=.07 for brain changes. To determine associations between changes in symptoms and changes in neural/molecular reward response in the estradiol treatment group, intercorrelations will be examined in primary analyses. A sample of 43 participants will yield 80% power to detect medium-to-large effects, with the smallest detectible effect size of *r*=.41.

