### Objectives {7}

The primary endpoints of the PEEPs study are mechanistic, measured via neural and molecular reward responses. Using simultaneous PET-MR imaging, this study will examine striatal blood oxygen level-dependent (BOLD) activation to rewards, measured with fMRI, and reward-related striatal dopamine release, measured with [^11^C]raclopride PET. To elicit a reward response, participants will complete a monetary incentive delay (MID) task during imaging. This task has previously shown sensitivity to altered reward-related dopamine release in a transdiagnostic anhedonia sample [35]. The first study objective aims to characterize the relationship between striatal reward responses and perimenopausal-onset anhedonia and psychosis symptoms at baseline. We hypothesize that anhedonia symptoms will be linked to reduced striatal BOLD activation and decreased task-related dopamine release to rewards. In contrast, we expect psychosis symptoms will be linked to increased striatal activation to rewards and higher baseline (tonic) dopamine release. The second objective of this trial will be to determine the effects of estradiol versus a placebo on perimenopausal-onset anhedonia and psychosis symptoms as well as striatal reward responses. We expect the effects of estradiol will be greater than placebo, as indexed by alleviation of anhedonia and psychosis symptoms and normalization of striatal reward response. We further hypothesize that reductions in *anhedonia* symptoms in the estradiol treatment group will be linked to increased striatal activation and increased dopamine release to rewards, whereas reductions in *psychosis* symptoms will be associated with decreased striatal activation to rewards and reduced tonic dopamine release.

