## Statistical methods

### Statistical methods for primary and secondary outcomes {20a}

The first objective of this study is to examine baseline (i.e., pre-treatment) associations between anhedonia and psychosis and neural and molecular responses to rewards. Associations between clinical measures and mechanistic outcomes will be estimated via correlation analysis. The second objective is to evaluate the experimental effects of estradiol versus placebo on clinical outcome measures and mechanistic outcomes. Mixed effects models will be used to examine the effects of time, treatment group, and their interaction on clinical outcomes (four timepoints, random intercept and slope) and neural and molecular outcomes (two timepoints, random intercept only), with age as a covariate. A separate model will be generated for each clinical outcome measure (anhedonia and psychosis) and each neural and molecular outcome (activation during reward anticipation and BP_ND_ and task-related ΔBP_ND_ for striatal regions of interest). Exploratory whole-brain analyses will also be conducted for fMRI activation during reward anticipation. Within the estradiol treatment group only, we will examine how biomarkers of reward response predict changes in clinical outcome measures. We will examine intercorrelations between anhedonia or psychosis and neural and molecular reward response, using residualized gain scores to quantify changes in clinical measures. We will also use mixed effect models to examine how changes in neural and molecular reward response predict variability in clinical outcome trajectories, with a separate model for each clinical outcome and each neural and molecular change score. Maximum likelihood estimation will be used in all mixed effect models to accommodate missing data (e.g., SAS proc mixed). When multiple comparisons are conducted to test a hypothesis, appropriate correction will be applied to achieve a corrected *p*-value of 0.05. For clinical outcome hypotheses, both a per-protocol and an intent-to-treat analytic approach (e.g., utilizing all available data, even for participants who did not finish treatment to completion) will be used. For mechanistic hypotheses, a per-protocol approach will be used, including only participants who completed the baseline PET-MR scan, 3 weeks of estradiol treatment, and the post-treatment PET-MR scan.

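### The two correlation power figures rest on different, unstated conventions: r=.27 at n=85 has 80% power only one-sided (71% two-sided), r=.41 at n=43 only two-sided, and neither allows for the promised multiplicity correction

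*Protocol article*

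**What the plan says.** Sample size {14} gives two power statements for correlations.

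- **Objective 1** (baseline symptoms against baseline neural and molecular markers): 85 participants "will yield approximately 80% power to detect small-to-medium effects (smallest detectible *r*=.27) at *α*=.05". The section adds that this agrees with the team's own pilot data.
- **Change on change, estradiol arm only:** "A sample of 43 participants will yield 80% power to detect medium-to-large effects, with the smallest detectible effect size of *r*=.41". The significance level is not restated.

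Neither statement says whether the test is one- or two-sided, and no other section does. The analysis section says only: "Associations between clinical measures and mechanistic outcomes will be estimated via correlation analysis".

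Objectives {7} words the hypotheses directionally. For anhedonia at baseline: "We hypothesize that anhedonia symptoms will be linked to reduced striatal BOLD activation and decreased task-related dopamine release to rewards". Psychosis is expected to go with higher activation and higher baseline (tonic) release. The hypotheses about change within the estradiol arm also carry a direction for each symptom.

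On multiplicity, Statistical methods {20a} says: "When multiple comparisons are conducted to test a hypothesis, appropriate correction will be applied to achieve a corrected" p-value of 0.05. Under Mechanistic outcomes: "For both neural and molecular measures, regions of interest will include the nucleus accumbens, caudate nucleus, and putamen".

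**The concern.** A reader who meets a significance level of .05 with no qualifier will take it as two-sided. On that reading the objective 1 figure is about nine percentage points too high. The natural defence is that a one-sided test was meant. That defence meets the second figure in the same section, which works only two-sided.

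Both figures also assume that each correlation is tested alone at 5%, while the plan commits to a correction when several comparisons test one hypothesis. The power of the analysis as planned is therefore lower than either figure.

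Objective 1 is one of the trial's two stated aims. If the expected correlation is near .27, the stated sensitivity is too favourable, and a non-significant result would be weaker evidence than a reader of this section would suppose.

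**Working it through.** **Inputs.** From Sample size {14}: n=85, r=.27, alpha=.05, power about 80%; and n=43, r=.41, power 80%. From Mechanistic outcomes: three regions per measure. From Objectives {7}: each symptom is linked to two measures (anhedonia to activation and task-related release, psychosis to activation and tonic release). Sidedness and correction method are not given, so both are varied below.

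**Formula.** For one Pearson correlation by Fisher's z, power = Φ(atanh(r)·√(n−3) − z_crit), with z_crit = 1.960 two-sided or 1.645 one-sided.

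**Step 1. The objective 1 figure.** atanh(.27) = 0.2769 and √82 = 9.055, product 2.507.

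- One-sided: Φ(2.507 − 1.645) = Φ(0.862) = 80.6%. This reproduces the plan's figure.
- Two-sided: Φ(2.507 − 1.960) = Φ(0.547) = 70.8%. This does not.

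**Step 2. The n=43 figure.** atanh(.41) = 0.4356 and √40 = 6.325, product 2.755.

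- Two-sided: Φ(2.755 − 1.960) = Φ(0.795) = 78.7%.
- One-sided: Φ(2.755 − 1.645) = Φ(1.110) = 86.7%.

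**Step 3. Does the choice of method matter?** Four variants were compared:

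| Method | n=85, r=.27, two-sided | n=85, r=.27, one-sided | n=43, r=.41, two-sided | n=43, r=.41, one-sided |
|---|---|---|---|---|
| Fisher z | 70.8% | 80.6% | 78.7% | 86.7% |
| Fisher z, bias-corrected, t-based critical value | 71.2% | 81.0% | 79.5% | 87.3% |
| Fixed predictor, noncentral t | 72.4% | 82.1% | 82.1% | 89.5% |
| Exact bivariate normal | 71.3% | 81.1% | 79.6% | 87.5% |

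On every method, r=.27 fits 80% only one-sided and r=.41 only two-sided. Rounding does not close the gap: r=.2749 at n=85 has 73% two-sided power.

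**Step 4. Detectable correlation at 80% power.** r = tanh((z_crit + 0.842)/√(n−3)).

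- n=85, two-sided: tanh(2.802/9.055) = tanh(0.309) = .30.
- n=85, one-sided: tanh(2.486/9.055) = tanh(0.275) = .27.
- n=43, two-sided: tanh(2.802/6.325) = .416 (.412 bias-corrected).
- n=43, one-sided: tanh(2.486/6.325) = .374 (.370 bias-corrected).

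For 80% two-sided power at r=.27, n = 3 + (2.802/0.2769)² ≈ 105 to 106.

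**Step 5. The promised correction.** The family is taken per hypothesis: 3 tests if a hypothesis is one symptom with one measure across three regions, and 6 if it is one symptom with its two measures (2 × 3). Bonferroni is an assumption.

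| Tests per hypothesis | Two-sided z_crit | Power, n=85, r=.27 | Detectable r, n=85 | Power, n=43, r=.41 | Detectable r, n=43 |
|---|---|---|---|---|---|
| 1 (as stated) | 1.960 | 71% | .30 | 79.5% | .41 |
| 3 | 2.394 | 55% | .34 | 65% | .47 |
| 6 | 2.638 | 45% | .37 | 55% | .50 |

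A one-sided test does not remove this gap. At .05/3 one-sided, z_crit = 2.128 and Φ(2.507 − 2.128) = 65%. At .05/6, z_crit = 2.394 and Φ(2.507 − 2.394) = 55%.

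**The case against.** **Sidedness.** The strongest reply is that the objective 1 figure is ambiguous rather than wrong. Its hypotheses all carry a direction, and a one-sided 5% test gives 81%. This stands as far as it goes. A reader might infer that r=.27 is an impossible figure, and the document does not support that. What the reply cannot explain is the n=43 figure, whose hypotheses are equally directional and which fits only a two-sided test.

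**Sample size at baseline.** Trial design {8} expects at least 85 women with two scans each, so more may have a usable baseline scan. With all 100 enrolled, two-sided power at r=.27 would be 78%. This is fair, but the stated figure is explicitly based on 85.

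**Family size.** A reader might cross three measures, three regions and two symptom scales, count 9 or 18 tests, and report much lower power. The plan corrects within a hypothesis, and Objectives {7} links each symptom to two measures, so 3 to 6 tests is what the document supports. Bonferroni is also conservative for correlated striatal regions. The choice of correction method, and any ranking of regions or measures, may properly be left to a statistical analysis plan.

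**The mixed-model figures.** A reader might suspect the f² values of .05 and .07 as well. Their definition and the within-person correlation are not given, so no error can be shown.

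**Consequence.** Nothing in the protocol says that a null result would be taken to exclude r=.27. The harm is an overstated sensitivity, not a planned misreading.

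**Conclusion.** The point holds, as a matter that should be fixed. At n=85 and 5%, power at r=.27 is 71% two-sided and 81% one-sided. At n=43, power at r=.41 is 79.5% two-sided and 87% one-sided. The two figures cannot share a convention, and the protocol declares none. This conclusion needs only the stated inputs and a test of a single correlation against zero.

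The r=.27 figure is stated at .05, and r=.41 reproduces at an unadjusted two-sided .05, so neither includes the promised correction. The corrected figures in the working (power of 55% to 45% at r=.27) rest on two assumptions: Bonferroni, and 3 to 6 tests per hypothesis. They are a conservative range rather than the plan's actual power.

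The uncorrected discrepancy is modest, .30 against .27, and trial conduct does not depend on it. The documents do not support going further and saying that the sample size must rise or that multiplicity is uncontrolled.

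**What to change.** In Sample size {14}:

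1. State the sidedness once, for all figures.
2. Then take one of two routes. Either restate objective 1 as a smallest detectable r of about .30 (two-sided .05, n=85) and keep r=.41 for n=43; or declare and justify one-sided testing, keep r=.27, and restate the n=43 figure on the same basis (about .37).
3. Say that these figures are before multiplicity correction, and add the detectable r at the corrected level for the planned family. If that were Bonferroni over 3 to 6 two-sided tests, the values would be about .34 to .37 at n=85 and .47 to .50 at n=43.

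The cost is a few sentences and slightly less favourable stated figures. No extra patients are needed, and no trial procedure changes.
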